#### Lung cancer screening

Health service organizations participating in the project will evaluate all their patients with current or past history of cigarette smoking for LCS eligibility according to CMS criteria through the EHR [55]. For those eligible for LCS, their provider will initiate a SDM discussion with the patient that will be documented prior to referral. Following SDM counseling, patients who are interested in LCS will be referred to the UT Health ET Lung Nodule Program for screening and navigation to any follow-up procedures indicated (e.g., diagnostic testing, cancer treatment). Services for UT Health ET patients will be billed to the patients’ insurance; additionally, this project will provide funding for LCS for 50 uninsured FCC patients annually (150 total) through the UT Health ET Lung Nodule Program, where patients will receive support for diagnostic testing, surveillance, and treatment when indicated. Figure 2 illustrates the pathways of provider and patient engagement in the program.

**Fig. 2 Fig2:**
[figure not shown]
This figure illustrates the workflow of the program, outlining key processes for providers and patients in the Lung Health Program for Northeast Texas. Arrows indicate the sequence of the activities, and different colors represent different pathways for patients eligible and not eligible for lung cancer screening

#### LCS and SDM training

Providers will receive training on LCS and SDM in a manner that works best for their respective units, which will be determined within the exploration phase of this project. Various materials and resources were previously developed by the project team and Decision Science Core to train care providers, who showed large gains in core knowledge of lung cancer and eligibility for screening [56]. These resources will be leveraged for use in the current program, including various decision support tools and materials to facilitate delivery of high-quality SDM for LCS, an online eligibility calculator for determining pack-year smoking history [57], a video and printed patient decision aid, and discussion guides about LCS for use during provider encounters.

#### Community engagement

Broader community dissemination is an important goal of this work. To raise awareness of LCS and LCS eligibility in Northeast Texas communities, we will reach people through community engagement strategies, including through health fair engagements, community town halls, and health ministry collaborations, where we will engage and educate adults, providing them with lay-friendly and diversity-tailored health education materials on tobacco use cessation resources and LCS information. Various local, non-profit community organizations will be contacted with information about the program, LCS eligibility, and with health education materials that can be used to educate their clientele. We will leverage health education materials previously developed by the project team for this purpose.

#### Technical assistance

A step-by-step implementation and sustainment guide describing the enacted hybrid approach to LCS will be disseminated via email to leadership at healthcare systems and clinics across Texas. We will offer hands-on technical assistance to interested parties who wish to implement the whole or constituent parts of the program based on their needs or capacity.

## Implementation strategies and approach

Implementation strategies were selected following the Expert Recommendations for Implementing Change (ERIC) taxonomy guide [58] to support the implementation process and ensure it is tailored to the context and target recipients [59, 60]. The operationalization of the strategies is guided by the EPIS framework, which outlines four main phases of the implementation process: *exploration*, which involves assessing the needs, understanding the setting dynamics, workflow, facilitators, and barriers; *preparation*, focused on building capacity, developing resources, and setting expectations; *implementation*, which involves delivering the intervention, while monitoring fidelity and addressing any unanticipated challenges by using audit and feedback procedures to share providers’ progress; and *sustainment*, aimed at maximizing impact and continued use of intervention after the active implementation work is completed via iterative stakeholder consultations focused on quality assurance [36, 58, 61]. Table 2 outlines the key implementation strategies and their alignment with each phase of the EPIS framework.

**Table 2 Tab2:** Implementation process components and objectives for the Lung Health Program for Northeast Texas

Phases of Implementation (EPIS)	Implementation Strategies and Components	Objectives
Exploration	Conduct local needs assessment; Complete pre-implementation surveys to assess for readiness and identify barriers and facilitators	Establish baseline knowledge, needs, barriers, and demographics for health service organization and participating clinics
Preparation	Sign Memorandum of Understanding between implementation participants	Achieve mutual understanding of process and expectations
	Organize internal implementation teams	Establish internal teams to support implementation and coordination between participants
	Develop a formal implementation blueprint with specific timeline	Discuss and set concrete steps for implementation; engage stakeholders in planning the program
	Provide technical assistance	Align internal systems with program expectations (i.e. EHR)
	Training programs preparation	Adapt training programs and dissemination materials to ensure responsiveness to local needs
	Develop education and dissemination materials	Provide access to resources to support implementation participants to deliver the program
Implementation	Conduct ongoing training in evidence-based tobacco cessation and SDM for LCS	Increase knowledge and skills required to implement the program, enhance self-efficacy of implementation participants
	Audit and provide feedback	Identify areas for further improvement and highlight successes; address barriers as needed
	Provide technical assistance	Provide support and consultations to healthcare partners to resolve issues that could delay the implementation
	Provide feedback	Support ongoing efforts to facilitate sustainability of the program and quality improvement opportunities
Sustainment	Provide technical assistance and training to community organizations	Maintain engagement and improve self-efficacy
	Provide continuous training opportunities	Support continuous learning and engagement to maintain knowledge and self-efficacy overtime
	Provide continuous training opportunities	Support continuous learning and engagement to maintain knowledge and self-efficacy overtime

During the *exploration* phase, we will assess participating organizations for readiness, identify barriers and facilitators, and conduct local needs assessment. These implementation strategies are selected to provide a better understanding of the inner and outer settings’ dynamics and workflow and evaluate the degree of readiness to implement the program. This formative process will also provide practical information needed to implement the program, such as the alignment of stakeholders’ EHR systems with data collection needs, including the documentation of smoking cessation care and SDM for LCS.

In the *preparation* phase, the research team will prepare healthcare leadership for active implementation by sharing an explicit summative document of program components, timeline, and expectations and assisting them in establishing internal implementation teams to ensure an effective execution of the project. A formal implementation blueprint will be tailored to participants’ needs and finalized during this phase.

Main strategies employed in the *implementation* phase will include ongoing training, technical assistance and consultation, and audit and feedback. Providers will receive training to screen for tobacco use, provide brief evidence-based motivational interviewing, cessation care, and relapse prevention interventions and quitline referrals, assess eligibility and facilitate SDM for LCS screening. Project partners will receive educational materials about smoking cessation and relapse prevention benefits for patients and clinical tools for providers. Audit and feedback procedures will include reviewing project documentation and patient data monthly and sharing findings with the leadership and providers to identify areas for further improvement and highlight successful elements of ongoing implementation on a quarterly basis. The project team will provide ongoing technical assistance and consultation to healthcare partners. Booster trainings to support staff and ensure their self-efficacy with care provision and referral processes will be provided as needed.

Data-driven adaptations to program implementation and materials will be used to maximize impact and identify mechanisms for *sustainment* of the intervention. Regular audits will ensure maintenance of procedures and inform feedback to leadership with recommendations for continued sustainment. Facilitation of learning opportunities, identification of local champions, and alignment of LCS and tobacco cessation care with existing quality improvement initiatives will support a continued uptake and sustainment of the program across participating sites.

### Dissemination

Dissemination strategies, aimed to achieve broader community engagement and increase awareness of tobacco intervention resources and LCS, are informed by Brownson et al. [62] and the utilization-focused surveillance framework for knowledge diffusion [63]. The dissemination plan comprises both passive and active strategies and entails the use of best practices for dissemination, including consideration of context, message, source, audience, and channel [62, 64, 65]. To reach *academic audience*, we will use open access publications and presentations. *Clinical and professional stakeholders* will be reached through targeted presentations, including webinars. To disseminate the program to *healthcare agencies*, we will use a step-by-step implementation and sustainment guide that includes a discussion of barriers to dissemination; a description of personnel and necessary resources to overcome barriers to program implementation; a description of expected outcomes; evaluation strategies with a sample evaluation plan; brief user-friendly case studies and narratives from our implementation experiences; FAQs; provider materials for point-of-decision use prompting; and quality management for sustainment. *Patient-facing* health promotion materials and patient decision aids relevant to tobacco use treatment and LCS will be developed and made available to community members. *Community* engagement strategies will include attendance of health fairs, virtual or onsite meetings with community groups, health ministry collaborations, regular newsletter distribution, and so on to provide lay-friendly and diversity-tailored health education materials for these audiences.

### Project goals and evaluation objectives

The current project has four overarching goals, each with several objectives. Table 3 describes program implementation goals and associated evaluation objectives, along with the types of data collected and their sources.Goal 1: Provide evidence-based tobacco use screening and cessation care for adult patients who smoke cigarettes. The objectives associated with Goal 1 are to ensure that 1) all participating providers receive at least one continuing medical education training to address tobacco use; 2) all adult patients who meet eligibility for LCS, currently use tobacco, and are interested in quitting are referred for tobacco cessation services through the MD Anderson Quitline and 15% of engaged patients achieve abstinence; and 3) all adult patients who currently use tobacco and are interested in quitting but do not meet eligibility for LCS are referred to the Texas Tobacco Quitline for tobacco cessation services.Goal 2: Provide SDM about LCS to all qualifying patients. Goal 2 objectives address LCS and include 1) continuing medical education about SDM for LCS to all participating providers; 2) SDM counseling for LCS to all eligible patients who are referred for LCS; and 3) 50% of patients referred for their first LCS complete it.Goal 3: Promote the program to community stakeholders and disseminate to healthcare systems and clinics. Objectives of Goal 3 involve 1) reaching community members with information about LCS eligibility and availability through passive and active dissemination of the program information and 2) contacting healthcare systems and clinics about the program with our implementation and sustainment guide and providing hands-on technical assistance and resources to support self-led implementation of program components in new healthcare systems and clinics.Goal 4: Navigate patients with abnormal screenings to diagnostic testing; those with cancer into treatment. Goal 4 includes two objectives that will ensure that 1) all patients whose screenings are abnormal will be navigated to and receive diagnostic testing and 2) all patients diagnosed with cancer and requiring cancer treatment will be navigated into treatment.

**Table 3 Tab3:** Implementation of a Hybrid Lung Health Program for Northeast Texas: goals, data types and sources, and evaluation objectives

Goal	Data Collected	Data Source(s)	Evaluation Objective
1. Provide evidence-based tobacco use screening and dependence care for adult patients who smoke cigarettes	Number of providers who attend an education session	MD Anderson project team records	All primary care providers from the target departments and clinics participate in ≥ 1 training (virtual or in-person)
	Number of patients referred to cessation services	EHR records; MD Anderson project team records	100% of patients who currently smoke and are interested in quitting are referred to a quitline
	Number of LCS-eligible patients engaged in MD Anderson Quitline who are abstinent at end of treatment	MD Anderson Quitline team records	15% of engaged patients will achieve abstinence
2. Provide SDM about LCS to all qualifying patients	Number of providers who attend an education session	MD Anderson project team records	All providers from the target departments and clinics participate in ≥ 1 training (in-person or virtual)
	Number of patients with a documented SDM visit before first LCS	EHR records from UT Health East Texas and Family Circle of Care	100% patients who meet eligibility for LCS receive SDM for LCS
	Number of patients completed first LCS	EHR records from UT Health East Texas Lung Nodule Program	50% of referred patients complete first LCS
3. Promote the program to community stakeholders and disseminate to healthcare systems and clinics	Number of community members reached	MD Anderson project team records	Reach ≥ 180 community members through > 18 activities (e.g., event attendance, newsletters, etc.)
	Number of healthcare clinics/systems received technical assistance	MD Anderson project team records	Contact >/= 90 healthcare systems/clinics (e.g., emails, in-person visits, mail-outs)
			Provide technical assistance to support self-led implementation of >/= 1 program component/s in >/= 2 new healthcare systems/clinics
4. Navigate patients with abnormal screenings to diagnostic testing; those with cancer into treatment	Number of patients navigated to diagnostic testing after abnormal LCS results	EHR records from UT Health East Texas Lung Nodule Program	100% of patients with abnormal results navigated to diagnostic testing
	Number of patients diagnosed with lung cancer navigated to treatment	EHR records from UT Health East Texas Lung Nodule Program	100% of patients with cancer navigated into treatment

*EHR* Electronic Health Record, *LCS* Lung Cancer Screening, *SDM* Shared Decision Making

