## Background

Lung cancer remains the leading cause of cancer-related mortality in the US and globally, with > 125,000 Americans dying from lung cancer annually [1]. Over 80% of lung cancer-related deaths are attributed to cigarette smoking, underscoring the importance of smoking cessation as a critical strategy to reduce the burden of lung cancer. Currently, ~ 11.5% of American adults smoke conventional cigarettes [2]. An effective strategy for reducing lung cancer mortality is screening persons with a history of heavy cigarette smoking using low-dose computed tomography (LDCT) imaging. Landmark trials, including the National Lung Screening Trial (NLST) [3] and the NELSON trial [4], have demonstrated that screening using LDCT imaging can significantly reduce lung cancer mortality through early detection. The US Preventive Services Task Force (USPSTF) currently recommends annual LDCT screening for individuals aged 50–80 years with a 20 pack-year smoking history who currently smoke or quit within the past 15 years [5]. The Centers for Medicare & Medicaid Services (CMS) covers lung cancer screening (LCS) with LDCT imaging, with a slight modification for eligibility (aged 50–77). Additionally, CMS mandates patient counseling about smoking cessation and shared decision making (SDM) using a patient decision aid before screening [6]. SDM counseling’s aim is to inform patients about risks and benefits of LCS and help them make a decision that aligns with their values and preferences. It also provides an opportunity to deliver evidence-based smoking cessation interventions to patients who smoke cigarettes, which are not otherwise consistently offered by providers at every healthcare encounter as recommended by clinical guidelines [7].

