## Methods

### Project goals and objectives

The overall goals of this project are to: (1) empower healthcare providers to screen patients for tobacco use and connect those interested in quitting with evidence-based cessation care; (2) support providers to engage in SDM counseling about LCS to all patients who meet eligibility criteria; (3) raise community awareness about LCS and LCS eligibility in Northeast Texas and actively disseminate the program to non-participating healthcare systems and clinics; and (4) navigate patients with abnormal LCS results to additional diagnostic testing and/or treatment, as needed. This work is guided by the Exploration, Preparation, Implementation and Sustainment (EPIS) framework [36], which provides a structured, systematic approach to identifying and addressing contextual barriers to evidence-based care at multiple levels, including those related to the outer context and inner contexts of the participating healthcare centers. This framework has been effectively applied to guide and evaluate implementation efforts within community-based healthcare settings, enhancing the understanding of processes and outcomes associated with implementation activities that involve collaborations between diverse stakeholders [36–38]. The program is additionally informed by Social Cognitive Theory (SCT), which emphasizes the reciprocal relationship between personal, behavioral, and environmental factors in shaping health-related behaviors [39]. SCT provides a framework for understanding and addressing key determinants of tobacco cessation and LCS participation, such as self-efficacy, outcome expectations, and social support that empower individuals to take an active role in their lung health, and their providers to actively participate in their care provision. Prior studies show that tobacco cessation education programs can contribute to increased tobacco-related knowledge among healthcare providers [40–42] and more consistent provision of tobacco cessation care overall [43–48].

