### Hybrid lung health program core intervention components

The current protocol will use a hybrid delivery model to complement the extant Lung Nodule Program at UT Health ET by leveraging existing strengths at MDACC in training providers for SDM for LCS and in the provision of evidence-based tobacco cessation interventions. This approach combines benefits of a centralized LCS model, represented by the UT Health ET Lung Nodule Program, and those of decentralized models, where some elements of LCS are delivered by primary care providers (see Table 1). Providing SDM at the level of primary care settings addresses one of the concerns about a centralized model of LCS delivery, where SDM is delivered by the LCS program staff immediately before the LDCT appointment. Existing evidence suggests that SDM counseling is more meaningful and beneficial if it is provided before people reach LCS centers, improving access and ensuring a better uptake of screening, which is particularly important in settings serving rural populations [51]. The following aspects of the program will be delivered partly or completely virtually and are denoted* in Table 1: training in SDM and tobacco cessation interventions for providers; provision of SDM (may include virtual aids); provision of smoking cessation interventions for LCS eligible patients who smoke; community outreach, and continuing education. Core intervention components follow.

**Table 1 Tab1:** Structure for the Lung Health Program for Northeast Texas

Program Component	UT Health East Texas & Family Circle of Care	MD Anderson Cancer Center
Identification of eligible patients for LCS	Implemented by participating providers though EHR	Provides tools for eligibility assessment (e.g. pack-year history calculator)
Training in SDM for providers*	Participating providers receive the training	MD Anderson Decision Support Lab provides in-person and on-demand SDM training
Provision of SDM about LCS for eligible patients*	Conducted by participating providers	MD Anderson Decision Support Lab provides patient decision aids; multiple formats and languages and low literacy materials
LCS results reporting; management of lung nodules and incidental findings; adherence to follow-up testing; adherence to annual screening	Conducted by UT Health East Texas Lung Nodule Program for all patients who complete LCS	n/a

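### The Goal 2 target for shared decision making is set on two conflicting denominators, all eligible patients and referred patients only, and the referred version cannot measure reach

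*Protocol article*

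**What the plan says.** All references are to the protocol article.

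- **Table 3, Goal 2, evaluation objective:** "100% patients who meet eligibility for LCS receive SDM for LCS". The denominator is all eligible patients. The title of Goal 2 also speaks of every qualifying patient, and the second overall goal under Project goals and objectives is to "support providers to engage in SDM counseling about LCS to all patients who meet eligibility criteria".
- **Project goals and evaluation objectives, Goal 2, objective 2 (text):** "SDM counseling for LCS to all eligible patients who are referred for LCS". The denominator is eligible patients who have been referred.
- **Table 3, Goal 2, data collected, same row as the target:** "Number of patients with a documented SDM visit before first LCS". This is a count with no stated denominator.
- **Lung cancer screening (workflow):** for an eligible patient, "their provider will initiate a SDM discussion with the patient that will be documented prior to referral". Then: "Following SDM counseling, patients who are interested in LCS will be referred to the UT Health ET Lung Nodule Program".
- **Measurement and data collection:** the health record counts listed for Goal 2 are patients who receive SDM, are referred, and complete a first screen. The number eligible is not listed, although the Lung cancer screening section says eligibility is assessed through the record.

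**The concern.** The text presents Table 3 as the statement of its goals and evaluation objectives, so the two should give the same target. They give different ones, and the choice between them can decide the conclusion.

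In this workflow SDM comes first and referral follows only for those who are interested. Referred patients are by design a subset of those who already had SDM. A rate computed among them says whether referrals were made in the right order. It says nothing about eligible patients with whom no one raised screening. Delivery of SDM by primary care providers is a central decentralized part of the hybrid model, so its reach among eligible patients is what the goal is about. If the definition stays open, the same data could be reported as a clear miss or as full success, and the denominator could be chosen after the results are known.

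**Working it through.** The 100% is a performance target, not a derived figure, and the article gives no sample size or patient counts for it, so there is nothing to reproduce. The check compares the two rates on one simple patient pathway.

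**Inputs**

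- From the article: SDM precedes referral, and only interested patients are referred afterwards (Lung cancer screening).
- Assumed, because the article gives none: E = 1,000 eligible patients; s = share of eligible patients who receive SDM (10%, 20%, 40%, 100%); a = share of SDM recipients who are interested and referred (50% to 80%); b = share of referrals made without documented SDM (0% or 5%).

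**Formulas**

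- Table 3 version: SDM recipients / eligible = sE / E = s.
- Text version: referred with SDM / all referred = 1 − b.

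The second formula does not contain s.

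**Results with E = 1,000**

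| s | SDM recipients | Referred after SDM (a = 50% to 80%) | Table 3 rate | Text rate, b = 0% | Text rate, b = 5% |
|---|---|---|---|---|---|
| 10% | 100 | 50 to 80 | 10% | 100% | 95% |
| 20% | 200 | 100 to 160 | 20% | 100% | 95% |
| 40% | 400 | 200 to 320 | 40% | 100% | 95% |
| 100% | 1,000 | 500 to 800 | 100% | 100% | not applicable |

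With b = 0% the two versions differ by 100% − s: 90, 80 or 60 percentage points in the first three rows. They agree only when every eligible patient receives SDM.

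**Check on the numerator.** Patients who have SDM and decline screening are never referred. With s = 20%, that is 200 − 160 = 40 to 200 − 100 = 100 patients. If only SDM recipients who go on to referral were counted, the rate among eligible patients would be 100/1,000 = 10% to 160/1,000 = 16%, against a true reach of 200/1,000 = 20%. A sound definition must count those who decline.

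**Check on the data.** The Table 3 version needs the number eligible. The Goal 2 record counts in Measurement and data collection (SDM, referred, completed) supply the text version's denominator but not Table 3's.

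**The case against.** Four points can be made for the plan.

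1. **The documents mostly point one way.** The overall goal, the Goal 2 title and the Table 3 target all refer to every eligible patient; objective 2 in the text is the outlier. This stands. It makes the repair easy, but it does not remove the conflict, because objective 2 is itself a formal statement of the target.

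2. **The referred measure can fail.** A reader might infer that it is 100% by construction. The documents do not support that: the workflow is an intended sequence, not an enforced gate, and any referral without documented SDM lowers the rate. The measure is a usable fidelity check. What it cannot detect is failure to reach eligible patients.

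3. **There are two stated denominators, not three.** A reader might take the data item ("Number of patients with a documented SDM visit before first LCS") as a third population, patients who go on to a scan. The patient entries in that column are plain counts, and the denominator sits in the evaluation objective column, as in the next row on completion. It is better read as a numerator with a timing condition.

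4. **SDM by screening staff is not shown to be counted.** A reader might infer that the timing condition lets in the practice "where SDM is delivered by the LCS program staff immediately before the LDCT appointment". That phrase describes centralized models in general. Table 1 assigns SDM to participating providers, the workflow places it before referral, and the data source for this row is the records of the two health organizations, whereas the completion row uses those of the Lung Nodule Program. Some overlap is possible, since Pulmonary Medicine at the hospital system takes part, but the documents do not establish it.

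It is also fair to say that this is one of several descriptive program targets, with no hypothesis test specified for it.

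**Conclusion.** The concern holds as a contradiction between two statements of the same target. Table 3 uses all eligible patients; objective 2 in the text uses only those referred. When the stated workflow is followed, the referred version is near 100% whatever share of eligible patients received SDM, so it measures compliance and not reach.

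The conflict itself is read directly from the article and needs no assumption. The size of the gap does: the article gives no number eligible, SDM rate, interest rate or bypass rate, so 60 to 90 points is an illustration for assumed reach of 40% down to 10%. A reader might infer that most eligible patients will go without SDM; nothing in the documents says so. The arithmetic shows only that the referred measure would not reveal it.

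Severity: should be fixed. It can reverse the conclusion on SDM reach, but it affects one descriptive target and the repair is small.

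**What to change.** - In Goal 2, objective 2 of the text, delete the qualifier that limits the objective to referred patients, so that text and Table 3 share one denominator: all patients identified as LCS-eligible through the health record at participating clinics.
- Add the number of eligible patients to the Goal 2 data in Table 3 and in Measurement and data collection.
- Define the numerator as every eligible patient with SDM documented by a participating provider: before referral if the patient is referred, and counted equally if the patient declines screening and is never referred. Reword the Table 3 data item to match, since a patient who declines has no first screen for the visit to precede.
- Report SDM among referred patients separately, labelled as a workflow compliance check.

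The cost is a wording change and one denominator query in a record that already assesses eligibility. The reported rate will probably be lower than the referred-only rate. The definition should be settled before results are seen.
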